#### Individuals who have been offered but not received ICJ

A stratified sample based on gender, age, cancer type and socio-demographic band will be developed based on the ‘individuals who have used ICJ’ sample. The service will also post the study pack on behalf of the research team to this sample alongside a reminder that ICJ is still available to them should they so wish.

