**Fig. 1 Fig1:**
[figure not shown]
Holistic Needs Assessment- The Concerns Checklist

Through administering a HNA the link officer can devise an individualised care plan and provide guidance and support to the person affected by cancer in order to access local services in relation to their needs. The link officer revisits each case approximately every 4 to 6 weeks, (or sooner depending on need) closing the case when they agree with their client that they require no further assistance from the service. The service also offers support to carers. For the purposes of this research a ‘carer’ refers to anyone who cares unpaid for the person with a cancer diagnosis. For example, this may be their spouse, friend or next of kin.

Improving the Cancer Journey (ICJ) was launched in February 2014 with a pilot phase focusing on five cancer groups. This service was then extended to all cancer types. It has been commissioned for 5 years. As of July 2016 the service has supported 1801 people. 52 % are female and 48 % are male. It supports most people in the 50–64 age bracket and 93 % of those who have accessed the service identify as having a white ethnicity. The most common primary diagnosis is lung cancer, followed by breast cancer.

This research was commissioned to focus on *impact* and *process* issues relevant to a) the individuals in receipt of the service, b) the service providers, and c) the wider culture. This research runs alongside the life of the programme for the next 5 years and is designed to draw out learning from the programme in an ongoing way.

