### Recruitment

#### Individuals who have used ICJ

At the initial meeting where the HNA takes place individuals are asked for their consent to share their data. For those who have consented ICJ keep a record of contact details for all their clients. All individuals who meet the inclusion criteria will be invited to participate. Participants will receive a study pack through the post. This will contain a welcome letter, participant information sheet, consent form and questionnaire booklet. If they wish to take part they will be provided with a stamped addressed envelope to return the questionnaire and consent form.

A final question on the questionnaire asks if they wish to take part in follow up interviews with a researcher. If they do, they will be asked to provide their contact details so the researcher can arrange this. The research team will recruit patients and carers this way. In year one the target is to interview 20 patients and carers who have used ICJ and indicated on the questionnaire that they wish to take part. We will purposively seek to recruit consenting participants who have experienced a wide range of outcomes as evidenced in their questionnaire responses. We will target different cancers and cancer stages to help obtain a broad sample. Written informed consent will be obtained for all interview participants. The process will be repeated at 2.5 and 4 years.

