#### Power analysis

There is no evidence to support effect size estimates so a moderate effect size of ICJ (d = 0.5) was adopted. Alpha was set to 0.0167 to allow for testing three different hypothesised mean differences (Hypotheses 1–3) on the same samples. With power set at 95 % this returned an estimated required total sample size of 264 (132 in each group) using G*Power version 2.

For the fourth hypothesis (self-reported experience of ICJ will be associated with scores on quality of life measures, patient activation scores and support) we ran an exact test on G*Power (version 2) running a correlation: bivariate model with the following assumptions: one tailed, hypothesised correlation 0.3, alpha error .05, power 95 %. This returned a sample size of 115. Whilst we hope to obtain a larger sample in order to conduct subgroup analyses, the required sample appears achievable.

The data will first be tested for outliers using boxplots and for normality using QQ plots. If normality is found, homogeneity of variance between groups will be tested with Levene’s test. Subsequent calculations will be based on the outcomes of these assumption tests. If normality and homogeneity of variance are established mean scores (from the PAM-13, FACT-G, EQ5-D and the MOS Social Support Survey) will be compared between the ICJ and non-ICJ group using *t*-test. If normality and/or homogeneity of variance cannot be established, a corresponding nonparametric method will be employed.

*Objective 2: To understand the process of ICJ as experienced by:*○ Patients and carers in receipt of the service○ The service providers, and○ The wider culture

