This protocol has limitations. We acknowledge Glasgow’s distinctive demography and the impact this may have on the generalizability of the findings. This is why we have proposed to evaluate the service from three levels; patient/carer, link officer and wider stakeholders to examine both individual and cultural factors to determine what factors are unique to the local area, what elements may be transferable and how this corresponds to wider findings relating to how and why this service may improve the lives of those affected by cancer. For comparative purposes we will distribute the questionnaire to a matched sample of individuals who also live in Glasgow, have been offered the ICJ service but decided not to take it up. As this sample live in Glasgow it minimizes any possible confounding variables from, for example, recruiting individuals who are cared for under a different health board. We hypothesise that those who have used the service with have significantly better outcomes than those who have not. However, we do not know why this group of individuals decided not to take up the service. It is possible that they are already well supported meaning there will be no difference in their outcomes. We will explore their reasons for not taking up the service along with descriptive statistics to provide further context to these findings.

Health policy in many countries has prioritised detecting and screening for psychological needs relating to cancer. Yet, despite this, distress is very common in those affected by cancer, across diagnoses and the disease trajectory. This service takes a proactive approach to screening drawing on a psychosocial holistic model of care to offer everyone in the city of Glasgow a personalised assessment right from diagnosis until whatever point that individual decides they no longer require the support. It is this element of care that is unique. The personalised approach provided by the link officers is at the centre of this service. Consequently, a key part of this research will focus on their experiences delivering the service. This will gather evidence that highlights how their skills and interactions with their clients shape the service but also how the service managers can support the link officers. This may be through the identification of training needs or recognition of the need to incorporate regular supervision into their working pattern to cope with the demands of working in an emotionally charged environment.

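### Comparators are balanced to ICJ users when packs are posted, but returned questionnaires are compared with a test that ignores the balancing factors, so postal response that differs by stratum between the groups can undo the balance

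*Protocol article*

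**What the plan says.** - **Building the comparison group.** Under Recruitment, the section on people offered but not receiving ICJ states: "A stratified sample based on gender, age, cancer type and socio-demographic band will be developed based on the" sample of people who have used ICJ. It continues: "The service will also post the study pack on behalf of the research team to this sample". Stratification therefore comes before posting. No stratum quota, replacement or top-up is described.
- **ICJ users.** The matching Recruitment section says "All individuals who meet the inclusion criteria will be invited to participate". Of those who wish to take part, it says "they will be provided with a stamped addressed envelope to return the questionnaire and consent form". Entry to the data set is by voluntary postal return.
- **Description of the comparators.** The Discussion says "For comparative purposes we will distribute the questionnaire to a matched sample of individuals who also live in Glasgow".
- **Target.** The Power analysis section gives an "estimated required total sample size of 264 (132 in each group"). Only completed questionnaires can meet it. No number of packs and no expected response rate is stated.
- **Analysis.** The same section fixes a t-test between groups on each scale, replaced by a nonparametric method if normality or equal variance fails. Those checks are the only things that change the method. No stratifier or weight enters.

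**The concern.** The four factors were judged important enough to shape the mailing list, yet they play no part after the packs leave. Balance on a posted list carries over to the returned questionnaires only if response by stratum follows the same pattern in both groups. There are reasons to doubt that here. Users have met a named link officer. Comparators did not take up the service's offer, and their pack comes from that same service with a reminder that the offer stands.

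If, say, one age or deprivation stratum returns fewer packs among comparators but not among users, the analysed groups differ in composition, and an unadjusted test reads that as an effect of ICJ. This is separate from self-selection into the service: it would arise even if uptake were random. At stake are the error rate of Hypotheses 1-3 and how far the word "matched" describes the data analysed.

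**Working it through.** **1. The plan's own figure.** Inputs from the Power analysis section: d = 0.5, alpha 0.0167, power 95%, equal groups. For a two-sided two-sample t-test with n per group, df = 2n - 2 and noncentrality = d × √(n/2). At n = 132 the noncentral t gives power 0.9502; at n = 131 it gives 0.9486. So 132 per group, 264 in total, reproduces exactly. The figure counts completed questionnaires and says nothing about their composition.

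**2. How response shifts composition.** Take one two-level stratifier posted 50:50 in both groups, with response r₁ and r₂ in its two levels. The share of level 1 among returns is r₁/(r₁ + r₂). If the levels differ by D standard deviations on the outcome, the spurious group difference is D × (share in users - share in comparators). All response rates and values of D below are assumptions; the documents give none.

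**3. False-positive rate.** This is the probability of rejection at 132 per group and two-sided alpha 0.0167, by noncentral t, with the true effect zero and the spurious difference as the shift.

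| D | User response, level 1 / 2 | Comparator response, level 1 / 2 | Level 1 share, users v comparators | Spurious difference (SD) | False-positive rate |
|---|---|---|---|---|---|
| any | 50% / 50% | 30% / 30% | 50% v 50% | 0 | 1.67% |
| 0.3 | 60% / 40% | 40% / 20% | 60% v 66.7% | 0.02 | 1.8% |
| 0.6 | 20% / 30% | 15% / 30% | 40% v 33.3% | 0.04 | 2.3% |
| 0.6 | equal | 20% / 30% | 50% v 40% | 0.06 | 3.0% |
| 0.6 | equal | 15% / 30% | 50% v 33.3% | 0.10 | 5.7% |
| 0.8 | 50% / 50% | 40% / 20% | 50% v 66.7% | 0.13 | 9.4% |
| 0.6 | equal | 10% / 30% | 50% v 25% | 0.15 | 11.9% |

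Example, fifth row: 0.15/(0.15 + 0.30) = 0.333, and 0.6 × (0.5 - 0.333) = 0.10 SD.

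The first row shows the condition. Response of 50% against 30% overall, even across strata within each group, leaves balance and error rate intact.

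**4. The template is ambiguous.** The ICJ-user sample used as template could be the users invited or the users who replied. If it is those who replied, comparators still start balanced only at posting, and even identical stratum response shifts them. With 50% / 40% response in both groups, users return 0.5/(0.5 + 0.4) = 55.6% level 1. Comparators posted at that mix return (0.556 × 0.5)/(0.556 × 0.5 + 0.444 × 0.4) = 61.0%.

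**5. Top-ups and weights must not be combined.** Take the fifth row. Topping up means posting 2:1 in favour of the poorly responding level, which brings comparator returns to 50:50. Weighting those returns by 1/0.15 and 1/0.30 then gives a 67:33 mix against the users' 50:50. That is 0.6 × 0.167 = 0.10 SD again, in the opposite direction. Inverse-response weights restore the mix that was posted, and top-ups deliberately unbalance that mix.

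**The case against.** The strongest reply is that the harm is conditional and its size unknown. It needs stratum-specific response to differ between the groups, and the larger figures come from unfavourable cases in which user response is flat and comparator response varies two- to threefold. When users share much of the gradient (third row), the shift is 0.04 SD. Even 0.15 SD is modest against the planned d of 0.5. This stands: the evidence supports saying that balance can be lost, not that it will be.

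Three stronger readings are tempting and not supported:
- A reader might infer that the Discussion claims matching removes confounding in the analysed data. It credits reduced confounding to residence in Glasgow, and "we will distribute the questionnaire to a matched sample of individuals who also live in Glasgow" claims matching at distribution only, which is accurate.
- A reader might divide 132 by the number in "As of July 2016 the service has supported 1801 people" and call the result a response rate. That number is people supported, not people who consented to data sharing, met the criteria and were mailed. The article also hopes for more than the minimum.
- A reader might infer that comparators are certainly drawn without regard to who replied. The template wording leaves open that responding users are already the basis.

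It can also be said that non-response handling belongs in a full protocol or analysis plan not shown. That holds for response tables. It does not cover the analysis, because the article does not leave adjustment open: it fixes an unadjusted comparison. Nor does it cover the order of mailing, which no later analysis plan can reverse.

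**Conclusion.** The point holds in conditional form. Balance is set at posting, data come from returns, and the stated test uses none of the stratifiers. Any between-group difference in stratum-specific response therefore passes straight into the Hypothesis 1-3 results. Under the assumed patterns the spurious difference is about 0.02 to 0.15 SD and the false-positive rate about 2% to 12% against 1.67%. These rest on one two-level stratifier, outcome gaps of 0.3 to 0.8 SD and response rates that are not in the documents. The true size could be nil. The point is worth acting on because the remedy is cheap and the mailing order cannot be changed afterwards. Confidence is medium.

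**What to change.** 1. **Recruitment.** State that the template is the ICJ questionnaires actually returned. Post ICJ packs first, draw comparators to that mix, and send top-up comparator packs in strata that fall short. Use broad strata: a full cross-classification of four factors is too sparse for 132 returns per group.
2. **Analysis.** Replace the unadjusted Hypothesis 1-3 comparison with a regression model containing group and the four stratifiers, with robust standard errors. Show the unadjusted result beside it. Do not apply inverse-response weights on top of the top-up mailing (step 5 of the working).
3. **Reporting.** Have the service supply anonymous counts of packs posted and returned by broad stratum for both groups. Give standardised differences for the returned samples. Call the groups matched only as far as these show it.

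The cost is a few weeks between mailings, some extra postage and a small loss of degrees of freedom. The change corrects imbalance on the four measured factors. It does not address self-selection into ICJ or non-response linked to unmeasured factors, and the write-up should say so.

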#### Link officers

The research team will provide an information session for the 7 link officers to detail the study aims and what their contribution will be. This will be supplemented with a participant information sheet. This process will be managed sensitively. As the link officers are closely aligned to this service they may find it difficult to say no to participation. Therefore, we will encourage them to take time over their decision and discuss it will their line manager. As with all participants we will remind them that they may withdraw at any point and this will not affect their working environment in any way. Written informed consent will be obtained for all those who wish to take part.

### Analysis

*Objective 1 - Identify the impact of ICJ on those diagnosed with cancer*

Hypotheses are:Individuals who have engaged with ICJ will report significantly different mean scores on patient activation measures than those who have not.Individuals who have engaged with ICJ will report significantly different mean scores on quality of life measures than those who have not.Individuals who have engaged with ICJ will report significantly different mean scores on social support than those who have not.Self -reported experience of ICJ will be significantly associated with scores on quality of life measures, patient activation scores and support.

#### Power analysis

There is no evidence to support effect size estimates so a moderate effect size of ICJ (d = 0.5) was adopted. Alpha was set to 0.0167 to allow for testing three different hypothesised mean differences (Hypotheses 1–3) on the same samples. With power set at 95 % this returned an estimated required total sample size of 264 (132 in each group) using G*Power version 2.

For the fourth hypothesis (self-reported experience of ICJ will be associated with scores on quality of life measures, patient activation scores and support) we ran an exact test on G*Power (version 2) running a correlation: bivariate model with the following assumptions: one tailed, hypothesised correlation 0.3, alpha error .05, power 95 %. This returned a sample size of 115. Whilst we hope to obtain a larger sample in order to conduct subgroup analyses, the required sample appears achievable.

The data will first be tested for outliers using boxplots and for normality using QQ plots. If normality is found, homogeneity of variance between groups will be tested with Levene’s test. Subsequent calculations will be based on the outcomes of these assumption tests. If normality and homogeneity of variance are established mean scores (from the PAM-13, FACT-G, EQ5-D and the MOS Social Support Survey) will be compared between the ICJ and non-ICJ group using *t*-test. If normality and/or homogeneity of variance cannot be established, a corresponding nonparametric method will be employed.

*Objective 2: To understand the process of ICJ as experienced by:*○ Patients and carers in receipt of the service○ The service providers, and○ The wider culture

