**Methods:**

The aim of this study is to understand if and how the service impacts upon the experiences and outcomes of people living with and affected by cancer. The study uses a sequential mixed methods design across a 5 year time point. Data gathering includes questionnaires, interviews, observations and reflective diaries. Participants include people affected by cancer who have used the service, a comparative sample who have not used the service, individuals who deliver the service and wider stakeholders. Outcomes include measures of patient activation, quality of life, health status, and social support. Data collection occurs at baseline, 2.5 years and 4 years with data from observations and reflective diaries supplemented throughout.

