### Aim and objectives

The overarching aim of this study is to understand if and how ICJ impacts upon the experiences of people living with and affected by cancer. There are 2 objectives:To identify the impact of ICJ on those diagnosed with cancerTo understand the process of ICJ as experienced by○ Patients and carers in receipt of the service○ The service providers, and○ The wider culture.

Hypotheses are:Individuals who have engaged with ICJ will report significantly different mean scores on patient activation measures than those who have not.Individuals who have engaged with ICJ will report significantly different mean scores on quality of life measures than those who have not.Individuals who have engaged with ICJ will report significantly different mean scores on social support than those who have not.Self -reported experience of ICJ will be significantly associated with scores on quality of life measures, patient activation scores and support.

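### Alpha is divided by three for Hypotheses 1–3, but the same section compares four scores between the groups, so 0.0167 does not guarantee the intended 5% family-wise error rate

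*Protocol article*

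**What the plan says.** The Power analysis section of the protocol article sets the significance level with an explicit reason: "Alpha was set to 0.0167 to allow for testing three different hypothesised mean differences". It ties those differences to "Hypotheses 1–3) on the same samples". On effect size, "a moderate effect size of ICJ (d = 0.5) was adopted". The result is given as: "With power set at 95 % this returned an estimated required total sample size of 264 (132 in each group".

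Later in the same section, the description of the group comparison lists what will be compared by t-test (or a nonparametric counterpart): "mean scores (from the PAM-13, FACT-G, EQ5-D and the MOS Social Support Survey". That is four scores.

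The hypotheses under Aim and objectives, repeated under Analysis, cover patient activation, quality of life and social support. The second reads: "Individuals who have engaged with ICJ will report significantly different mean scores on quality of life measures than those who have not". Under Measures, the Quality of life heading holds two instruments, FACT-G and EQ-5D. The eligibility text on patients offered but not receiving ICJ names four domains to be compared: activation, quality of life, health status and support.

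The article names no lead score for Hypothesis 2, gives no rule for combining FACT-G and EQ-5D, and makes neither of them secondary.

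**The concern.** The article chose 0.0167 for one purpose: to hold the overall error rate when several mean differences are tested on the same people. A Bonferroni divisor does this only if it equals the number of tests in the family. Here the divisor is three, while the listed comparisons number four. The fourth arises because the quality-of-life domain has two instruments.

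Two things follow. The 5% family-wise limit is no longer guaranteed, and the stated power is for an alpha that does not match the listed tests. There is also a problem of interpretation. A significant result on either FACT-G or EQ-5D could be reported as support for Hypothesis 2, and nothing says what to conclude if the two disagree. The Discussion expects the findings to bear on the service's sustainability and on policy, so it should be clear which test carries the claim.

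This is not a detail that an article can be expected to leave to an analysis plan. The article itself states the alpha, the reason for it and the list of scores, and these do not agree.

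**Working it through.** **Inputs, all from the protocol article**
- Standardised difference d = 0.5, power 95%, 1:1 groups, alpha 0.0167 per test (Power analysis).
- Two-sided testing, because the hypotheses speak of different means (Aim and objectives).
- Scores compared: 4 (Power analysis).
- Correlations between scores: not given, so any value used below is an assumption.

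**Step 1. Reproduce the stated figure.**
0.05/3 = 0.0167.
Power of the two-sample t-test comes from the noncentral t with df = 2n − 2 and noncentrality d√(n/2). For n = 132, df = 262 and noncentrality = 0.5 × √66 = 4.06.
At two-sided alpha 0.0167, power = 95.0%, and 132 is the smallest n that reaches 95%. Total = 2 × 132 = 264, an exact match.
The normal approximation gives 131 per group. A one-sided test gives 115 per group (230 in total) and does not reproduce the figure. The stated sample size is therefore right for its own inputs.

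**Step 2. Count the tests.**
- Hypothesis 1: PAM-13.
- Hypothesis 2: FACT-G and EQ-5D, both under the Quality of life heading.
- Hypothesis 3: MOS-SSS.

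Total: 1 + 2 + 1 = 4. Counting by the domains in the eligibility text (activation, quality of life, health status, support) also gives 4.

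**Step 3. Family-wise error at 0.0167 per test.**
Bound = k × 0.0167. Under independence the rate is 1 − (1 − 0.0167)^k.

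| Tests | Bound | Independent |
|---|---|---|
| 3 | 5.0% | 4.9% |
| 4 | 6.7% | 6.5% |

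For four correlated test statistics (simulation, 1,000,000 draws, common correlation assumed):

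| Assumed correlation | Family-wise rate |
|---|---|
| 0.3 | 6.2% |
| 0.5 | 5.7% |
| 0.7 | 4.8% |

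If only FACT-G and EQ-5D are strongly correlated (0.7) and every other pair is at 0.3, the rate is 5.9%.

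**Step 4. Power and sample size at an alpha that matches four tests.**
0.05/4 = 0.0125. By the same noncentral t calculation, 132 per group gives 93.8% power, and 95% needs 139 per group, or 278 in total. The differences from the plan are 95.0 − 93.8 = 1.2 percentage points of power, or 278 − 264 = 14 participants.

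**The case against.** The strongest reply is that the plan intends three tests. The article several times lists health status as an outcome separate from quality of life. It describes EQ-5D partly as an index of health status and FACT-G as the validated quality-of-life measure, and no hypothesis mentions health status. On that reading, Hypotheses 1–3 map to PAM-13, FACT-G and MOS-SSS, with EQ-5D an extra comparison outside the confirmatory set, and 0.0167 is right. The plural in Hypothesis 2 does not settle the matter, because Hypothesis 1 also uses a plural although activation has only PAM-13.

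This reading is possible, but the article does not adopt it. EQ-5D is placed under the Quality of life heading, and the analysis text lists it on equal terms with the other three scores. The reply shows that a simple clarification would rescue the stated alpha. It does not show that the clarification has been made.

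It is also fair to say that the effect is small, that strong correlation between the scores could keep the true rate under 5%, and that the section hopes for more than the required number of participants. All of that stands and limits the weight of the point. But the article gives no correlations and does not rely on them.

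A reader might infer a larger problem from the Abstract: "Data collection occurs at baseline, 2.5 years and 4 years". Four scores at three waves would make twelve comparisons. The document does not support this. Nowhere does it say that the group comparison is tested at each wave, and how waves enter the analysis is commonly left to the full protocol or analysis plan. The point rests on the four scores alone.

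**Conclusion.** The point holds in a limited form. The calculation itself is correct, but the divisor of three does not match the four between-group comparisons listed in the same section. A reader might take this to mean that the error rate certainly exceeds 5% or that the sample size is miscalculated. Neither follows. The excess is at most 1.7 percentage points (6.7% against 5.0%), it depends on correlations the document does not give, and the sample size is right for three tests.

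What can be said is that 5% is not guaranteed as written, and that 95% power at 264 belongs to three tests only. These conclusions assume two-sided testing, d = 0.5 for each score, and all four scores tested at 0.0167. The change is worth making because it concerns an alpha and a power that the article states, and because it would settle which score decides Hypothesis 2.

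**What to change.** Make one of two wording changes in the Power analysis section.

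1. Name either FACT-G or EQ-5D as the test of Hypothesis 2, and declare the other secondary, outside the confirmatory family. Alpha 0.0167, 95% power and 264 then stand unchanged. The cost is that one score can no longer support a confirmatory claim.
2. Keep all four scores as confirmatory, use alpha 0.0125 (or Holm's procedure over the four), and restate power as about 94% for 264. The cost is about 1 percentage point of stated power. If 95% is to be kept, the total rises to 278.

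Under option 2, also say whether Hypothesis 2 is supported by either quality-of-life score or only by both. Neither option changes the questionnaires or the data collection.

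### Hypotheses 1–3 have 0.0167 as their only stated significance level; the Bonferroni split is valid and correctly sized, but Holm's step-down rule would give the same 5% family-wise guarantee and is never less powerful at the same sample

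*Protocol article*

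**What the plan says.** All the relevant text is in the Analysis part of the protocol article, mostly under Power analysis.

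- Level: "Alpha was set to 0.0167 to allow for testing three different hypothesised mean differences", namely Hypotheses 1–3, measured on the same people.
- Effect, power and size: "a moderate effect size of ICJ (d = 0.5) was adopted"; "With power set at 95" per cent; the result is an "estimated required total sample size of 264 (132 in each group").
- Direction: the hypotheses are worded as differences, for example "Individuals who have engaged with ICJ will report significantly different mean scores on patient activation measures than those who have not". That implies two-sided tests.
- Comparison: "mean scores (from the PAM-13, FACT-G, EQ5-D and the MOS Social Support Survey") "will be compared between the ICJ and non-ICJ group using" a t-test, or a nonparametric test if its assumptions fail. This paragraph gives no significance level and no rejection rule.
- Hypothesis 4 is sized separately ("one tailed, hypothesised correlation 0.3, alpha error .05, power 95" per cent) and is outside the 0.0167 family.

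Neither Bonferroni nor Holm is named.

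**The concern.** If 0.0167 is the threshold for every comparison, the study uses a rule that another rule dominates on the criterion the split is meant to serve. Holm compares the smallest of three p-values with 0.05/3, the next with 0.05/2 and the last with 0.05, and stops at the first failure. Suppose one hypothesis has p = 0.001 and the next p = 0.02. The fixed threshold calls the second negative, while Holm rejects it because 0.02 is below 0.025. If two hypotheses are already rejected and the third has p = 0.04, Holm rejects that one too.

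The study states a separate hypothesis of a difference for activation, quality of life and social support. What is at stake is therefore power for each hypothesis and the chance of establishing all three. The article also says it had no evidence on which to base the effect size, so a true effect below 0.5 is possible, and the gain is larger there.

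**Working it through.** **Inputs from the Power analysis section.** d = 0.5, alpha 0.0167, power 95%, 132 per group. Sidedness is not stated there; two-sided follows from the wording of the hypotheses. **Assumption not in the document:** correlation between the three outcomes, taken as 0 to 0.5.

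**Step 1: reproduce 264.** The normal approximation is n per group = 2 × [(z for 1 − 0.0167/2 + z for 0.95) / d]² = 2 × [(2.393 + 1.645)/0.5]² = 130.5, so 131. The noncentral t calculation gives 132 per group, 264 in total, with power 95.0%. One-sided versions give only 114 (normal) or 115 (t). The stated size therefore reproduces, as a two-sided test.

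**Step 2: check the level.** 0.05/3 = 0.01667. Three tests at 0.0167 sum to 0.0501 (rounding). If they are independent, the family-wise error is 1 − (1 − 0.0167)³ = 4.93%.

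**Step 3: Bonferroni against Holm at 132 per group.** Three z-statistics, each with mean d × √(132/2), so 0.5 × 8.124 = 4.06 at d = 0.5, were simulated 400,000 times. Tests were two-sided at family level 0.05. Paired entries are for correlation 0 / 0.5.

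| True effects | Measure | Bonferroni | Holm |
|---|---|---|---|
| d = 0.5 on all three | per hypothesis | 95% | 98.1% / 97.7% |
| d = 0.5 on all three | all three rejected | 86.4% / 88.7% | 94.7% / 95.1% |
| d = 0.4 on all three | per hypothesis | 80% | 88% / 87% |
| d = 0.4 on all three | all three rejected | 51.9% / 61.7% | 72.3% / 77.1% |
| d = 0.5 on two, none on the third | per true effect | 95.2% | 96.5% / 96.4% |
| d = 0.5 on one only | that hypothesis | 95.3% | 95.3% / 95.4% |
| none | any rejection | 4.9% / 4.5% | 4.9% / 4.5% |

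The chance of rejecting at least one hypothesis is the same under both rules, because both first compare the smallest p-value with 0.05/3.

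**Step 4: what Holm spends.** With two true effects and one null, the chance of wrongly rejecting the null is 1.7% under Bonferroni and 4.6–4.8% under Holm. With no true effects, the expected number of false rejections is about 0.050 under Bonferroni and 0.051–0.055 under Holm. Holm's extra power comes from using error that Bonferroni leaves unspent, within the 5% limit.

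**Step 5: the count.** Four scores are compared, while the alpha is split for three hypotheses; quality of life has both FACT-G and EQ-5D. If Holm is run over all four, its first step is 0.05/4 = 0.0125. Power for that step taken alone, at d = 0.5 and 132 per group, is about Φ(4.062 − 2.498) = Φ(1.564) = 94.1%, or 93.8% by noncentral t. That is slightly below the planned 95%.

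**The case against.** The strongest case against raising this is that nothing is wrong. Bonferroni is valid under any dependence, the split is correctly computed, and the planned 95% power per test is delivered. All of that stands.

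The figure 0.0167 also appears only as an input to the sample-size calculation. A reader might infer that the protocol commits itself to calling any p-value between 0.0167 and 0.05 negative. The text does not say so. The inference is natural, since the level is given as an allowance for testing and no other is offered. It is not forced, since Holm also starts at 0.05/3 and the same sizing fits it. Nor can the absence of a named procedure be counted as an omission, because a condensed article may leave it to an analysis plan that is not shown.

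A reader might also infer that Bonferroni gives up power and gets nothing in return. That is true of the family-wise guarantee only. Bonferroni also bounds the expected number of false rejections at 0.05 and comes with simple matching simultaneous intervals.

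Finally, the large gains need all three effects to be real. The Discussion section itself allows that the non-users may already be well supported and show no difference. This limits the size of the point but does not remove it: Holm is never less powerful than Bonferroni, whatever the truth.

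**Conclusion.** The point holds as an optional efficiency improvement, not as a correction. At the planned effect on all three outcomes, Holm adds about 2 to 3 points of power per hypothesis and about 6 to 8 points to the chance of confirming all three. At d = 0.4, a value assumed here and not given in the article, it adds about 15 to 20 points to the latter. With two true effects the gain is about 1 point per hypothesis, and with one about nil. It never changes the chance of rejecting at least one.

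These figures assume three tests, equal effects where present, two-sided testing, 132 per group and a correlation of 0 to 0.5. The documents do not support the stronger readings that the study is underpowered, that its error control fails because of Bonferroni, or that the sample size must change on account of this point. That four scores face an alpha split for three is a separate matter. It bears on this point only because Holm needs a defined family.

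**What to change.** Keep 0.0167 for the sample size. Add a sentence stating that Hypotheses 1–3 are judged by Holm's step-down procedure at a family-wise 5%, and report Holm-adjusted p-values.

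Define the family in the same place, in one of two ways:

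- name the one score, FACT-G or EQ-5D, that tests Hypothesis 2, so that three p-values enter; or
- apply Holm across all four scores, accepting a first step of 0.0125 and about 94% power at that step with 132 per group.

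Both statements should be fixed before the group comparisons are seen. Data collection does not change. The costs are that simultaneous confidence intervals will not match Holm's decisions exactly (Bonferroni intervals can still be shown, labelled as such) and that the expected number of false rejections is slightly higher, with the family-wise error still held at 5%.
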